A pilot study carried out in 2013 highlighted a mindfulness-based intervention for individuals with WS [13]. The practice of mindfulness is frequently used in CBT interventions. It teaches one to pay attention and to have moment-to-moment awareness [16]. This CBT treatment approach has been found efficacious in treating emotional disorders in individuals with WS. This pilot research took place in a 5-day institutional setting, and the long-term effects of the treatment were not evaluated. In addition, the application of treatment in a context of institutionalization raises the question of the generalization of the results and the autonomy of individuals with WS.

Another study was conducted in 2022, in which a group of 4 adults with WS were virtually delivered an adapted CBT intervention [17]. In this study, a CBT program was adapted for people with intellectual disability. Participants and caregivers in this study reported a high level of satisfaction and a reduction in their anxiety. This study provided support for the acceptability and feasibility of group-based CBT treatment for anxiety in WS. However, the sample size was small, and the methodology used did not have strong scientific reliability.

The objective of our study is to propose and discuss clinical interest in CBT with digital support for anxiety in people with WS, taking into account intellectual disability. Because of the rarity of WS, the single-case methodology seems appropriate. In addition, this methodology allows for analyzing the effects of the intervention at an individual level. The development of digital support will allow participants to perform the therapy exercises at home. This could be particularly interesting for people with intellectual disabilities who need to be assisted with the realization of a number of daily tasks. The objective of the digital support is to empower them. Furthermore, this application makes it possible for the patient to evaluate himself or herself from home on a daily basis, allowing an ecological repeated assessment. We hypothesize that patients with WS will be able to engage in an adapted CBT protocol. We hypothesize that individuals’ anxiety will decrease over the course of therapy. We also hypothesize that other factors such as QoL will be improved with this therapy protocol.

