### Participants

We will recruit 5 participants for this study. The inclusion criteria are age >18 years, molecular confirmation of WS, sufficient level of language assessed by a score >7 on the Clinical Evaluation of Language Fundamentals 4 test [23], and complaints of anxiety. The complaints of anxiety can be expressed by the individual or the individual’s representative. For the inclusion criteria in this study, we chose to evaluate this complaint with the following Likert scale completed by the participant: “This week I have been anxious” or “This week the individual has been anxious.” To be included in the protocol, the participant will need to score at least 1 on this self-rated Likert scale. We chose to include people with low anxiety as well as high anxiety, even if an anxiety disorder is not characterized, because anxiety is generally underestimated in WS, with one longitudinal study finding co-occurring anxiety in approximately 82% of patients with WS [24].

Exclusion criteria are uncorrected visual disturbance, uncorrected deafness, or being already treated for anxiety. Because of the intellectual disability, individuals with WS will be accompanied by a caregiver during visits requiring signing consent or a hetero-evaluation.

Individuals will be recruited from patient associations and among individuals followed in the medical genetics department of Montpellier University Hospital. Interested individuals will receive information about the study, first with a letter; then, they will be in contact with a doctor involved in the study to ask questions. Because of the rarity of WS, individuals recruited could live far from the hospital where the study is taking place. Financial support for travel costs will be offered to each individual taking part in this study. Individuals with WS who wish to be involved and a legal representative will sign written informed consent; then, the individual will be prescreened for inclusion and exclusion criteria.

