We will use the Tau-*U* to examine the within-phase trend and between-phase difference to estimate the treatment effect both within and between phases. We prefer the Tau-*U* to alternative statistics (ie, proportion of nonoverlapping data) because it provides a baseline trend–corrected estimation of trends in treatment and follow-up phases by combining nonoverlap between phases and trends within phases. The following 3 Tau-*U* indices will be calculated: (1) Tau-*U* A-to-A compares a phase-A score with another phase-A score, (2) Tau-*U* B-to-B compares a phase-B score with another phase-B score, and (3) Tau-*U* A-to-B compares a phase-A score with a phase-B score. The Tau-*U* A-to-B is similar to the Mann-Whitney *U* test for group independence, and a *P* value is produced in addition to an estimate of effect size. These Tau-*U* indices estimate the effect of the treatment on both within phase trends and between-phase differences. We will use the following 2 forms of the Tau-*U* indices: the uncorrected and corrected Tau-*U*. The corrected Tau-*U* estimates the degree of the baseline trend and adjusts baseline and treatment phase observations to remove the effect of the baseline trend. We will use the corrected Tau-*U* to estimate an effect size from the corrected data when the Tau-*U* A-to-A is significant [41]. We will use the Tau-*U* calculator web-based application [42].

We will estimate the reliability of change for our nomothetic outcomes using the reliable change index (RCI) [43]. The RCI measures in which direction an individual has changed and estimates whether this change is reliable and clinically significant. We will calculate the RCI statistic for the 3 dimensions of the French WHOQOL-BREF (physical health, psychological health, and social relationships) for which reliability coefficients are available [31]. For each of these 3 WHOQOL-BREF dimensions, we will calculate the value of the standard using our patients’ scores at baseline. A reliable change in both treatment and follow-up compared with baseline measures will be achieved with values ≥1.96.

Concerning the HAM-A, there is no fidelity index validated in French, which does not allow the calculation of an RCI value. The results obtained from this evaluation will therefore be used in a descriptive manner, in order to relate them to the repeated evaluations of anxiety that constitute our main evaluation criterion.

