A comparative table data will also be edited with the nomothetic outcome measures.

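### The reliable change index is said to speak to clinical significance although its 1.96 cut-off shows only change beyond measurement error, and the rule as printed has no limb for deterioration

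*Protocol article*

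**What the plan says.** The Introduction of the protocol article states a directional hypothesis for quality of life: "We also hypothesize that other factors such as QoL will be improved with this therapy protocol". The Data Analysis section gives the method for testing it in individuals: "We will calculate the RCI statistic for the 3 dimensions of the French WHOQOL-BREF", namely physical health, psychological health and social relationships.

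The index is described as follows: "The RCI measures in which direction an individual has changed and estimates whether this change is reliable and clinically significant". The spread in its denominator appears to come from the trial's own patients: "we will calculate the value of the standard using our patients’ scores at baseline". The decision rule is one sentence: "A reliable change in both treatment and follow-up compared with baseline measures will be achieved with values ≥1.96".

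The section then says that the HAM-A will be used descriptively, because no RCI can be calculated for it. It ends with a plan for a table: "A comparative table data will also be edited with the nomothetic outcome measures". The sample is small: "We will recruit 5 participants for this study". The article states no normative cut-off, functional threshold or minimal important difference for the WHOQOL-BREF.

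**The concern.** There are two problems in the same paragraph.

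1. **Interpretation.** The RCI compares an observed change with the change that measurement error alone could produce. Passing the threshold makes error an unlikely explanation. It says nothing about whether the change matters to the patient, which needs a separate criterion. The article attributes both properties to the one index.
2. **Direction.** The index is described as carrying direction, so it is signed. The threshold is printed only as a lower bound of 1.96. Read literally, a strongly negative value falls in the same class as no change.

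The RCI is the only decision rule stated for the quality-of-life hypothesis. With five participants, each person is 1/5 = 20% of the sample, so one reclassified participant visibly changes the summary.

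**Working it through.** **Inputs from the protocol article (Participants; Data Analysis).** Cut-off 1.96; three dimensions; five participants; two comparisons with baseline (treatment and follow-up).

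**Assumptions.** The article prints neither the RCI formula nor any SD or reliability coefficient. I use the usual form, RCI = (later score − baseline score) / S_diff, with S_diff = SD × √(2(1 − r)), and vary the reliability r from 0.6 to 0.9. Errors are taken as normal and S_diff as known.

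**Step 1: the plan's own figure.** The normal quantile at 0.975 is 1.95996, which rounds to 1.96. P(|Z| ≥ 1.96) = 0.0500 and P(Z ≥ 1.96) = 0.0250. So 1.96 is the two-sided 5% value, and the number is right for a symmetric rule.

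**Step 2: what the cut-off measures.** The smallest change that counts as reliable, in baseline SDs, is 1.96 × √(2(1 − r)):

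| Assumed r | Calculation | Smallest reliable change (SD) |
|---|---|---|
| 0.6 | 1.96 × √0.8 | 1.75 |
| 0.7 | 1.96 × √0.6 | 1.52 |
| 0.8 | 1.96 × √0.4 | 1.24 |
| 0.9 | 1.96 × √0.2 | 0.88 |

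The boundary doubles across this range (1.75 / 0.88 ≈ 2.0) purely because the reliability changes. Nothing in the formula refers to functioning, norms or patient-perceived importance.

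**Step 3: the printed rule against a symmetric rule.** Take a participant with RCI = −2.5. Under the literal rule, −2.5 is not ≥ 1.96, so the result is no reliable change. Under |RCI| ≥ 1.96, 2.5 ≥ 1.96, so the result is a reliable worsening.

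For a true deterioration of t standard errors of a difference, the literal rule flags with probability 1 − Φ(1.96 + t). The symmetric rule flags with probability [1 − Φ(1.96 + t)] + Φ(t − 1.96).

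| t | Literal rule | Symmetric rule |
|---|---|---|
| 2 | under 0.01% | 52% |
| 2.5 | under 0.01% | 71% |
| 3 | under 0.01% | 85% |

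The few flags under the literal rule would be false improvements. For a participant with no true change, the chance of a flag per comparison is 0.0250 under the literal rule, all on the improvement side. Under the symmetric rule it is 0.0500, or 0.0250 each way.

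**Step 4: number of classifications.** 5 participants × 3 dimensions × 2 comparisons = 30.

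**The case against.** The strongest reply concerns direction. The rule speaks of reliable change, not improvement. It contains neither a plus sign nor the word only. The preceding description says the index gives direction, so size and sign can be read as two outputs, with 1.96 applied to size. The value is the two-sided one. In a condensed article, a dropped absolute-value sign is at least as likely as a planned one-sided rule. The comparative table should still let a reader see a fall in score. All of this stands. A reader might infer that the plan is built to report benefit and hide harm, but the documents do not support that.

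Some of the direction point remains. The printed sentence has no negative limb, and the stated hypothesis is improvement. The commitment to report a contra-therapeutic direction is made for the repeated daily measures, not for the WHOQOL-BREF. A table of scores does not classify a worsening as reliable.

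On clinical significance, the reply is that this is one general sentence about the method, that it says the index estimates rather than proves, and that the operative rule uses only the word reliable. It is fair that no success claim is tied to 1.96. A reader might infer that every reliable improvement will be reported as clinical benefit, but the article does not say so. The sentence nevertheless attributes to the index a property that the stated criterion cannot deliver. It is an affirmative statement, not a detail left for a statistical analysis plan.

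**Conclusion.** The point holds in two parts of unequal strength. The description of the RCI as speaking to clinical significance is wrong for the rule given, because 1.96 marks change beyond measurement error and the article states no clinical criterion. The direction part is a wording defect: applied as printed, a reliable deterioration would be classed as no reliable change, but a symmetric rule may have been intended.

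The effect is confined to the secondary quality-of-life conclusion. The primary analysis of the daily anxiety item does not use the RCI. The SD-unit boundaries (0.88 to 1.75) rest on assumed reliabilities, and conversion to scale points would need further assumptions that the article does not supply. The detection probabilities in step 3 need no SD or reliability value, but they do assume normal errors and a known standard error of a difference.

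**What to change.** Three edits to the RCI paragraph in Data Analysis:

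1. Delete the reference to clinical significance and state that the RCI speaks only to change beyond measurement error. Alternatively, add a separate clinical criterion for each dimension, specified before the data are analysed.
2. Write the rule as |RCI| ≥ 1.96, with higher scores meaning better quality of life. Classify each participant and dimension as reliably improved (RCI ≥ 1.96), reliably worsened (RCI ≤ −1.96) or no reliable change (otherwise).
3. Apply and report this classification separately at end of treatment and at follow-up. The current sentence names the two together, and this removes any doubt about whether both are needed.

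The cost is a few sentences, with no new data and no change to the design. If a symmetric rule was intended, the second edit only records it. The small downside is that worsening becomes visible as its own category and no claim of clinical significance can be made from the RCI alone.

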## Results

As of spring 2019, the app was fully developed. Participant recruitment and data collection began in September 2019. Due to the COVID-19 crisis, data processing was postponed in 2022-2023, and it is projected that the study findings will be available for dissemination by summer 2023.

## Discussion

In this manuscript, we describe the research protocol for evaluating an anxiety therapy program for individuals with WS. WS is a rare genetic disease in which individuals present with intellectual disability of variable intensity but, in general, have good language skills. Most individuals with WS present with anxiety. Because of the rarity of WS, there is a lack of validated studies on the psychotherapy of anxiety in these individuals. Therefore, their anxiety is usually treated with medication, and the side effects are more severe than in the general population. However, some therapies have been found effective in individuals with intellectual disability. Because of their good language skills, such individuals could particularly benefit from psychotherapy.

This manuscript describes the research protocol to test the effectiveness of CBT for anxiety in individuals with WS. This protocol is based on the single-case and multiple baseline research methodology. This methodology is particularly interesting for 2 aspects. First, it is a scientific research method that applies to small samples (as few as 3 people), so it is a particularly interesting methodology for rare diseases. Second, this methodology enables consideration of interindividual variations by observing the results of each individual individually. It enables evaluation of the fluctuations of anxiety in the daily life of individuals. For this protocol, a smartphone app was developed. This app allows daily self-assessment of anxiety by the patients and can be a support mechanism for the therapy protocol. This app can be particularly helpful for a population with an intellectual disability, for whom the appropriation of certain CBT tools may be difficult.

However, this work has some limitations. First, regarding the app, some improvements might be possible. The developed app has not yet been validated from a psychometric point of view. It can only be used to assess the evolution of anxiety for each patient but cannot be used as a diagnostic tool.

In addition, this app makes it possible to store the participant's evaluation data and thus to know when the patient evaluated his or her anxiety, but there are no data to know how the participant used the other tools in the app (the therapy support tools). It would be interesting to integrate a module to know how often the participant uses the app for therapeutic purposes.

Finally, this protocol only includes a small sample of patients with WS. Depending on the results, it would be interesting to evaluate this protocol with patients with other pathologies.

## Abbreviations

CBT: cognitive behavioral therapy
CPP: committee of protection of people
HAM-A: Hamilton Anxiety Rating Scale
QoL: quality of life
RCI: reliable change index
WHOQOL-BREF: Abbreviated World Health Organization Quality of Life
WS: Williams syndrome
